### Participant timeline {13}

The main timeline may be found in Table 1, and timeline for the ancillary study in Table 2.

**Table 1 Tab1:** Time schedule SHIFT

	Study period				
	Enrolment	Operation	Months postoperatively		
Timepoint	***− X****	0	***3***	***12***	***36***
**Enrolment:**					
**Eligibility screening**	X				
**Informed consent**	X				
**Allocation**		X			
**Interventions:**					
***Stomal ultrasound***	X			X	X
***CT-scan***	X**			X**	X**
**Assessments:**					
***Clinical characteristics***		X	X	X	X
***EORTC CR29/CR30***	X		X	X	X
***VHPQ***	X		X	X	X

CT, computerised tomography

*Time from enrolment to operation will vary

**When clinical evaluation and stomal ultrasound is insufficient

**Table 2 Tab2:** Time schedule of ancillary study

	Study period					
	Preoperative	Operation	Postoperative			Analyses
Timepoint	***− 1 day***	0	***1 day***	***3 months***	***12 months***	***t***_***x***_
**Interventions:**						
***Fascia sample***		X				X
***Venous blood sample***	X	X	X	X	X	X
***Subgroup intervention:***						
***Needle biopsy***					X	X
**Assessments:**						
***List baseline variables***	X					
***List interventional variables***		X				

### Sample size {14}

The power calculation is based on the primary outcome with an estimated short-term complication rate of 15% in the FTSG-group and in 40% in the synthetic mesh group. To achieve 80% power and 95% significance level, 39 patients are required in each arm. To compensate for loss to follow-up over the relatively long follow-up time, we plan for 90 patients (45 in each arm) to be included in the trial.

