### Trial design {8}

The trial is a parallel group, superiority trial with an allocation ratio of 1:1.

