#### Rate of complications and recurrences

Data are presented descriptively and the results from each study group are compared with chi-squared test.

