#### Health economics

Data are presented descriptively and the results from each study group are analysed with Mann-Whitney *U* test or Student’s *t* test depending on the distribution of the specific variable.

The study assumes a significance level of 0.05.

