### Statistical methods to handle protocol non-adherence and missing data {20c}

Study outcomes are analysed as per protocol. Patients are randomised in the operating theatre after induction of general anaesthesia and the only scenario where the patient does not receive the intervention allocated is if it is deemed technically impossible after the laparotomy has been performed or if the patient suffers an anaesthetic complication before the randomisation envelope is opened. In both these scenarios, the patient cannot be operated with any intervention so chance should evenly distribute this specific form of non-adherence.

No statistical methods are used to compensate for missing data or loss to follow-up. The power calculation is dimensioned to enable enough statistical power with up to 12 missing patients in all.

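### The 39 patients per arm reproduce only as a one-sided 5% calculation; under the planned chi-squared test at 0.05, power is about 70% at 39 per arm and about 77% at the full 45 per arm, not 80%

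*Protocol article*

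**What the plan says.** All references are to the protocol article.

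- **Sample size {14}** takes an "estimated short-term complication rate of 15% in the FTSG-group and in 40% in the synthetic mesh group". It continues: "To achieve 80% power and 95% significance level, 39 patients are required in each arm". To cover losses, "we plan for 90 patients (45 in each arm) to be included in the trial".
- **Trial design {8}**: "The trial is a parallel group, superiority trial with an allocation ratio of 1:1".
- **Rate of complications and recurrences**, under the statistical methods, gives the test for the primary outcome: "Data are presented descriptively and the results from each study group are compared with chi-squared test".
- The significance level stands at the end of the **Health economics** paragraph: "The study assumes a significance level of 0.05".
- **Statistical methods to handle protocol non-adherence and missing data {20c}** relies on the sample size: "The power calculation is dimensioned to enable enough statistical power with up to 12 missing patients in all".

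No section says whether testing is one-sided or two-sided.

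**The concern.** A chi-squared test on a two-by-two table rejects for a difference in either direction, so at 0.05 it is a two-sided test. For 15% versus 40% at 80% power, 39 per arm is clearly too small for such a test. It is what one gets by putting the whole 5% in one tail.

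Two commitments depend on the figure. The enrolment target of 90 is 39 per arm plus an allowance for loss, and the tolerance for 12 missing patients is the difference between 90 and 78. If 39 is wrong, the trial has less power for its primary safety outcome than it claims, and the loss allowance does not exist. A non-significant result would then be read as coming from a trial with a 20% type II error when the true figure is nearer 30%.

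**Working it through.** **Inputs.** p1 = 0.15, p2 = 0.40, difference 0.25, 80% power (Sample size {14}); 1:1 allocation (Trial design {8}); alpha 0.05 (end of Health economics); chi-squared test (Rate of complications and recurrences). The sample size section's 95% level is read as alpha 0.05.

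**Formula.** Patients per arm, pooled variance under the null:

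n = [z_alpha × √(2·p̄(1−p̄)) + z_power × √(p1(1−p1) + p2(1−p2))]² / (p2 − p1)²

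- p̄ = (0.15 + 0.40)/2 = 0.275
- √(2 × 0.275 × 0.725) = √0.39875 = 0.6315
- √(0.1275 + 0.2400) = √0.3675 = 0.6062
- z_power = 0.8416 and (p2 − p1)² = 0.0625

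**Step 1: reproduce the protocol's 39 (one-sided 5%, z = 1.645).**
n = (1.645 × 0.6315 + 0.8416 × 0.6062)² / 0.0625 = (1.0387 + 0.5102)² / 0.0625 = 2.399 / 0.0625 = 38.4, rounded up to **39**.

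**Step 2: the same formula two-sided (z = 1.960).**
n = (1.2377 + 0.5102)² / 0.0625 = 3.055 / 0.0625 = 48.9, rounded up to **49**.

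**Step 3: does another formula explain 39?** Patients per arm at 80% power:

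| Formula | Two-sided 5% | One-sided 5% |
|---|---|---|
| Pooled | 49 | 39 |
| Unpooled | 47 | 37 |
| Arcsine | 48 | 38 |
| Pooled variance throughout | 51 | 40 |
| Pooled with continuity correction | 57 | 47 |
| Log odds ratio | 54 | 43 |
| Log relative risk | 59 | 47 |

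The smallest two-sided answer is 47, so the choice of formula does not account for 39.

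**Step 4: power of the two-sided test.** Power = Φ[(0.25·√n − 1.960 × 0.6315) / 0.6062].

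- n = 39: (1.5612 − 1.2377)/0.6062 = 0.534, power 70.3%
- n = 45: (1.6771 − 1.2377)/0.6062 = 0.725, power 76.6%
- n = 49: (1.7500 − 1.2377)/0.6062 = 0.845, power 80.1%

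Check by exact binomial enumeration of each test at 15% versus 40%:

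| Per arm | Normal approximation | Exact, uncorrected chi-squared | Exact, Yates | Exact, Fisher |
|---|---|---|---|---|
| 39 | 70.3% | 72.3% | 62.5% | 62.5% |
| 45 | 76.6% | 78.4% | 69.4% | 69.5% |
| 49 | 80.1% | 80.9% | 74.6% | 74.6% |

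**Step 5: the missing-data allowance.** 90 − 12 = 78 = 2 × 39. With 12 patients missing (evenly split), power is 70% to 72%, and the type II error is 28% to 30% instead of 20%.

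**Step 6: what effect would give 80% at 39 per arm?** With mesh held at 40%, the graft rate would have to be 12.5% by the formula, or about 13% by exact enumeration, not 15%.

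**The case against.** **Sidedness is inferred.** The protocol never says one-sided or two-sided, and its hypothesis is directional: the graft is expected to be safer. One could call this an undeclared one-sided calculation. That does not rescue the text. If a one-sided test was meant, the calculation and the chi-squared test planned at 0.05 use different error rates, and a correction is needed either way. A one-sided 5% level would also be hard to justify here.

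**The shortfall at full enrolment is small.** This stands. With 45 per arm and no loss, power is 1.6 points (exact) to 3.4 points (approximation) below 80%. The assumed rates are described as short-term, so losses at the assessment that matters may be few. However, the protocol attaches its 80% to 39 per arm and states no power for 90, and its missing-data section vouches for 78 patients. At 39 per arm the gap is 8 to 10 points.

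**The headline figures are the less favourable approximation.** Exact enumeration of the uncorrected test is about 2 points higher, and by that route 48 per arm already reaches 80.4%. Both sets of figures are given above, and neither brings 39 or 45 per arm to 80%.

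**Yates and Fisher are not in the protocol.** Correct. Their figures only show what is lost if a corrected or exact test is used instead.

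**The error is one of wording, without effect on type I error or estimates.** True, but it misstates a design property of the primary comparison and it set the enrolment target.

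**Conclusion.** The concern holds. With the protocol's own inputs, 39 per arm gives 80% power only at a one-sided 5% level that is nowhere declared. For the planned chi-squared test, taken as two-sided at 0.05, the requirement is 49 evaluable per arm (47 to 59 across formulas). Power is about 70% at 39 per arm (exact 72%) and about 77% at 45 per arm (exact 78%). Even complete follow-up of all 90 patients falls just short of 80%, so there is no reserve from which 12 could be lost.

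This rests on the assumed rates of 15% and 40%, equal arms, no continuity correction, and the two-sided reading of the chi-squared test.

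**What to change.** 1. In Sample size {14}, replace the statement about 39 per arm with, for example: *With a two-sided chi-squared test at the 5% level, without continuity correction, 45 evaluable patients per arm give about 77% power and 39 per arm about 70% to detect 15% versus 40%; 80% power needs 49 evaluable patients per arm.* If exact figures are preferred, use 78% and 72% and say so.
2. In the missing-data section {20c}, delete the claim that power remains sufficient with 12 patients missing.
3. In the statistical methods, state that the test is two-sided and uncorrected. Yates or Fisher would cost about 9 to 10 further points relative to the exact uncorrected figures (7 to 8 relative to the normal approximation).

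The cost is protocol wording and a less favourable stated power; no extra patients are needed. Two alternatives are open. The sponsor could raise the target to at least 98 evaluable patients (2 × 49) plus an allowance for loss. Or it could declare and justify a one-sided test consistently in the sample size and analysis sections, which would be difficult to defend.

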### Recruitment {15}

The surgeons responsible for the decision to operate on a patient with parastomal hernia will provide information about the trial.

Furthermore, stomal dressing and basic stomal care is provided by stoma nurses who meet all stoma patients. Since stoma-related complaints are usually first pointed out to the stoma nurse by the patient, information about the trial will be presented to the stoma nurses at each participating hospital. In this manner, any potential candidates for inclusion will be referred by the nurses to the assessing surgeon. To increase the rate of inclusion, other study centres will be invited to participate in the trial. The trial is advertised at conferences, meetings and other forums in which representatives from other potential study centres are present.

## Assignment of interventions: allocation

### Sequence generation {16a}

The randomisation sequence is arranged in blocks of five with alternating overweight to either allocation obtained manually by research administrators. This eliminates the risk of skewing distribution at centres with low case volumes.

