### Eligibility criteria {10}

Consultant surgeons with long experience in abdominal wall surgery will be responsible for the assessment of potential study participants before inclusion and will attend all intervention procedures.

Inclusion criteria:
Colo-, ileo- or urostomyParastomal hernia diagnosed with intrastomal ultrasonography and/or CT-scanSymptoms from the parastomal hernia requiring surgical intervention18 years of ageSufficient knowledge of the Swedish language assuring that questionnaires can be adequately understood and answered

Exclusion criteria:
Cognitive impairment causing poor compliance to postoperative prescriptions and/or answering questionnairesInsufficient amount of good quality skin suitable for transplantationExpected high donor-site morbidityFistula/e adjacent to stomaMb CrohnConcomitant ventral hernia requiring mesh repairOther intra-abdominal disease requiring surgical intervention

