### Concealment mechanism {16b}

A total of 90 opaque and sealed envelopes numbered 1 to 90, each containing a paper with either the word “FTSG” or “Synthetic mesh,” 45 of each. They are kept locked-in at the research group’s office upon the day of randomisation.

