### Implementation {16c}

The allocation sequence is generated by the research group administrators. Patients are enrolled by surgeons at the out-patient clinic and are provided a randomisation number correlating to a sealed envelope. The intervention arm is assigned after induction of anaesthesia when the accompanying randomisation envelope is opened.

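### Fixed blocks of five with an alternating majority make up to 30% of allocations certain to someone who knows the scheme and all earlier allocations, and do not support the claim that centre imbalance is eliminated

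*Protocol article*

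**What the plan says.** Sequence generation {16a} fixes the method: "The randomisation sequence is arranged in blocks of five with alternating overweight to either allocation obtained manually by research administrators". It then claims: "This eliminates the risk of skewing distribution at centres with low case volumes".

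Concealment mechanism {16b} describes "A total of 90 opaque and sealed envelopes numbered 1 to 90", 45 per arm, and says of storage: "They are kept locked-in at the research group’s office upon the day of randomisation". No section mentions stratification by centre or reserving blocks for centres, and none rules it out.

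Implementation {16c} sets the order of events: "Patients are enrolled by surgeons at the out-patient clinic and are provided a randomisation number correlating to a sealed envelope". The envelope is opened only after induction of anaesthesia. The footnote to Table 1 says that the interval from enrolment to operation varies.

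Eligibility criteria {10} makes experienced consultant surgeons responsible for "assessment of potential study participants before inclusion and will attend all intervention procedures". Who will be blinded {17a} lists operating surgeons as not blinded. Patients, postoperative care providers and the follow-up surgeon are blinded.

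**The concern.** Random allocation protects the comparison only if those who decide on entry cannot foresee the next arm. Here the block size never varies and the majority arm alternates, so the make-up of every block is known once the make-up of one is known. If the blocks run in number order, a patient's number also shows the place within the block. The people with discretion over entry are the people who see past allocations.

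Two exclusion criteria, too little suitable skin and expected high donor-site morbidity, are judgements whose practical consequence falls on the skin-graft arm alone. A surgeon who expects that arm next could, even without intent, apply them more strictly. Blinded outcome assessment does not undo selective entry.

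Separately, the protocol offers the blocks as a guarantee of balance at small centres. Blocks give that only if they are used within centres, and even then only approximately.

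**Working it through.** **Inputs.** Blocks of five with alternating majority ({16a}); 90 envelopes, 45 per arm ({16b}); three centres at first, with more to be invited (Study setting {9}, Recruitment {15}). Centre shares are not given and are assumed below.

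**The plan's own figure.** 90 / 5 = 18 blocks. Alternating 3:2 and 2:3 gives 9 × 3 + 9 × 2 = 45 per arm. This reproduces the stated 45:45.

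**Certainty under full knowledge.** A 3:2 block has 10 possible orders. An allocation is certain once one arm is used up.

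- Places 1 and 2: never certain.
- Place 3: certain if the first two were both from the minority arm, 1/10 = 0.1.
- Place 4: certain in 4 of the 10 orders, 0.4.
- Place 5: always certain, 1.0.
- Sum: 0.1 + 0.4 + 1.0 = 1.5 per block, so 1.5 / 5 = 30%, and 18 × 1.5 = 27 of 90.

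Always guessing the arm with more envelopes left in the block (a tie counts one half) is right with probability 0.6, 0.6, 0.7, 0.7 and 1.0 by place. The mean is 3.6 / 5 = 72%, against 50% without information.

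If the observer does not know which arm leads in the first block, that block yields 0.5 certain allocations and the other 17 yield 1.5 each: 0.5 + 17 × 1.5 = 26 of 90 (29%). A majority drawn at random for each block would give 0.5 / 5 = 10% throughout, so the alternation itself raises 10% to 30%.

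**Certainty under less knowledge.**

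| What the surgeon knows | Certain allocations |
|---|---|
| All earlier allocations | 30% |
| All but the latest one | (0.1 + 0.4) / 5 = 10% |
| All but the latest two | 0.1 / 5 = 2% |
| Shared list, own centre only, three equal centres | about 3% |
| Shared list, own centre only, shares 60/25/15 | 6% overall, 9% at the largest |
| Shared list, own centre only, shares 80/10/10 | 14% overall, 18% at the largest |

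The last three rows come from simulation with assumed centre shares.

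**Centre balance, one shared list.** If a centre's n patients fall at random places among the 90, the number allocated to one arm is hypergeometric (90 envelopes, 45 of that arm, n drawn).

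- n = 6, split 5:1 or worse: 2 × [C(45,5) × C(45,1) + C(45,6)] / C(90,6) = 126,248,430 / 622,614,630 = 20%.
- n = 10, split 7:3 or worse: the same sum over 7, 8, 9 and 10 in one arm gives 31%.

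**Centre balance, blocks reserved per centre.** If the majority also alternates within the centre, the difference between arms is at most 3 at any time and at most 1 after a completed block, so the 5:1 and 7:3 splits cannot occur. Imbalance still arises in part-used blocks: the first two patients share an arm with probability (3 + 1) / 10 = 40%, and the first three with probability 1/10 = 10%. If a centre received two blocks with the same majority, the difference could reach 4.

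**The case against.** The strongest reply is that the two sets of figures rest on opposite readings. With one shared list the poor centre splits apply, but 30% certainty then needs every centre's allocations in list order. With blocks reserved per centre, own-centre knowledge suffices for 30%, but the poor splits disappear. This is right, and the figures must not be added together. It does not rescue the text: one reading defeats the balance claim outright, and the other makes prediction easier and still leaves some imbalance.

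The second reply is timing. Eligibility is judged in the clinic, while envelopes are opened at surgery after a variable delay, so earlier envelopes may still be sealed. This also stands, and it is why 30% and 72% are upper bounds at enrolment. A reader might infer that surgeons will in practice know about 30% of allocations; the documents do not support that.

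Third, the sequence is made by administrators and kept locked away. But the article itself publishes the block size and the alternation. Knowledge can also cross centres: steering committee members are clinically active at the three initial centres, and a surgeon from an initial centre assists at the first operations of new ones.

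Fourth, Intervention description {11a} allows other donor sites, so a shortage of midline skin need not exclude a patient. That weakens the lever but leaves the judgement in place.

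Some stronger readings should be set aside. It would be wrong to call the trial unblinded, since patients, ward staff and the follow-up surgeon are blinded. A reader might also infer that patients lost before surgery use up the 90 envelopes, but nothing says that unopened numbers cannot be reissued. Whether centre belongs in the primary analysis is a separate question.

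**Conclusion.** The concern holds in a bounded form. The stated rule makes up to 30% of allocations (27 of 90) certain, and the best guess right up to 72% of the time, for someone who knows the scheme and all earlier allocations. The likely figure at enrolment is lower: 2–10% with one or two recent envelopes sealed, and about 3–18% with a shared list and own-centre knowledge under the assumed shares.

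The claim that skew at small centres is eliminated is unsupported on either reading. It fails clearly if the 90 envelopes form one shared series. It is too strong if blocks are reserved per centre. The single series is inferred from the 1-to-90 numbering and the silence on centres; it is not stated.

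Nothing here shows that selection has occurred. It is an avoidable weakness in a trial where entry involves judgement relevant to one arm.

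**What to change.** For all remaining allocations:

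- Replace the manual alternating blocks with a computer-generated sequence stratified by centre, with randomly varying block sizes not disclosed to surgeons.
- Take the next envelope in the centre's sequence in theatre, instead of tying a number to the patient in the clinic.
- Delete the sentence claiming elimination of skew, or soften it to say that blocking within centres limits imbalance.

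As an illustration, random block sizes of 4 and 6 make about 6% of allocations certain over the first 12 places, for an observer who knows the possible sizes, the start and all earlier allocations. The best-guess rate for that observer is still about 68%, so the gain is mainly in removing certainty, and non-disclosure matters. Fixed blocks of four would not help: 33% would be certain.

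The cost is a short amendment, a new list and new envelopes. Final arm sizes may differ from 45:45 by a few patients.

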### Concealment mechanism {16b}

A total of 90 opaque and sealed envelopes numbered 1 to 90, each containing a paper with either the word “FTSG” or “Synthetic mesh,” 45 of each. They are kept locked-in at the research group’s office upon the day of randomisation.

### Implementation {16c}

The allocation sequence is generated by the research group administrators. Patients are enrolled by surgeons at the out-patient clinic and are provided a randomisation number correlating to a sealed envelope. The intervention arm is assigned after induction of anaesthesia when the accompanying randomisation envelope is opened.

## Assignment of interventions: blinding

### Who will be blinded {17a}

The allocated intervention is blinded to the patient, postoperative care providers and the surgeon performing the clinical follow-ups. The operating surgeons and the data analysts are not blinded.

### Procedure for unblinding if needed {17b}

If a patient suffers a complication that requires reoperation, the surgeon on call can be unblinded to the procedure that has been performed if it is deemed necessary to assess the indication for surgical intervention. Reoperation does not necessarily necessitate unblinding of the patient and the nursing staff nor does the trial follow-up surgeon need to be unblinded to the index procedure that has been performed.

## Data collection and management

### Plans for assessment and collection of outcome data {18a}

All clinical study data will be registered in an Access® database (Microsoft, Redmond, WA, USA).
Baseline data are collected at the time of inclusion once assessment of eligibility by the including surgeon is complete. At this point, the surgeon is unaware of what intervention the patient will be allocated. Baseline data include:
BMI. Body mass index.ASA (American Society of Anesthesiologists) class.Current medical conditionsCurrent medicationNumber and type of previous abdominal surgeries.Type of and reason for stomaOperation data will be collected immediately after surgery by the surgeon. Data collected on completion of surgery:
Participating surgeonsTreatment allocationSize of the hernia defect before and after reductionSize of the FTSGLength of stoma bowel above the fasciaOperating timeMinimum overlap of reinforcement materialData on postoperative care on the ward will be collected by the blinded nursing staff on a case report form (CRF). After discharge, the CRF will be collected and registered in the database. Parameters monitored daily during the entire time on the ward:
C-reactive proteinSerum albuminComplete blood cell countSerum creatinineBlood glucoseOxygen saturationExperienced pain assessed on a visual analogue scaleClinical follow-up data will be collected by the blinded surgeon conducting the follow-up. This surgeon will be experienced in stoma surgery (i.e. colorectal, or abdominal wall surgery) but will not receive any specific training on the follow-up procedure in this study. Parameters that will be assessed at the clinical follow-up:
BMIClinically judged recurrenceSurgical complication (seroma, infection, other)Stoma complication (stenosis, necrosis, other)Readmission or reoperation during the follow-up periodPain assessed on a visual analogue scaleExperienced improvement assessed on a visual analogue scaleAbnormal healing process or poor aesthetic result of the operation scarCompliance to the postoperative girdle prescribedQuestionnaires both preoperative and during the follow-up period will be collected by the research group administrators and stored in a separate Access database. Questionnaires used in the study are:
VHPQ, which is a validated questionnaire specially designed to evaluate pain in relation to daily activities following ventral hernia repair. VHPQ was developed and validated by our research group and focuses on pain behaviour [18].EORTC C30 and CR29, questionnaires developed by the European Organisation of Research and the Treatment of Cancer, are used to explore and quantify different aspects of health-related quality of life (QoL) in patients with cancer. C30 constitutes the “core” questionnaire with a broad range of questions including social, emotional and physical aspects of cancer [20, 21]. CR29 focuses on symptoms specific for colorectal cancer and includes a section on stoma-specific problems [19]. These questionnaires are validated and shall be answered together. The questionnaires are interpreted with designated scoring manuals.

